### Analysis plan

Quantitative analysis will be performed using Stata, blind to allocated arm, and will follow the Statistical and Health Economics Plan approved by the independent Trial Steering and Data Management and Ethics Committees (TSC, DMEC). To be defined as having received RAFT, a patient in the intervention arm must have attended at least session 1. Data entry checks against 100% of questionnaires will be made by two researchers together.

*Clinical status analysis*: The primary intention-to-treat analysis will involve between-arm comparisons for the primary outcome fatigue impact (BRAF-NRS Impact) at 26 weeks, adjusted for baseline values. Analyses of covariance (ANCOVA) will use multivariable linear regression models and standardised effect sizes calculated (adjusted mean difference divided by pooled baseline SD), with >0.5 considered a clinically meaningful effect. Sensitivity analyses will be conducted by (1) additional adjustment for any variables displaying imbalance at baseline, (2) fitting multilevel mixed effects models to investigate any clustering effect from delivery in groups and centres, and (3) multiple imputation techniques to investigate the impact of missing data, based on 20 imputed data sets, with baseline fatigue severity, impact, pain and disease activity added to the imputation model as variables predictive of missingness.^62^ Secondary outcomes will be analysed in the same way, including analysis of the four BRAF-MDQ fatigue subscales, and preliminary multivariable analysis of different attendance rates/patterns.

Further analyses using repeated measures mixed effects ANCOVA models will examine the effect of interventions over time by including up to four follow-up scores (26, 52, 78, 104 weeks) for the primary outcome, adjusting for baseline scores. Convergence/divergence between trial arms over time will be investigated by including appropriate interaction terms in the model. Clustering effects will be investigated by including CB group and centre IDs as additional levels. We will examine (and if necessary, adjust for) possible differences between arms for RA medication changes. Where numbers allow, we will explore coefficients of predictors of outcome.

*Cost effectiveness analysis*: Actual expenses of training and delivery will be recorded. Unit costs for NHS staff time for training and intervention delivery will be based on national estimates and costs of medications; community, primary and secondary care during follow-up will be based on national tariffs,^63–65^ supplemented by micro-costing or local estimates. Productivity costs due to RA and fatigue will be estimated based on average weekly earnings stratified by age.^66^ Resource use will be combined with unit costs to estimate the incremental cost or savings of the group CB programme over the 2-year period. The primary analysis will be from the societal perspective, including productivity costs. Secondary analyses will restrict the perspective to NHS and personal social services costs.

EQ-5D-5L utility scores will be used to estimate Quality Adjusted Life Years (QALYs), adjusting for any baseline imbalances.^67^ Missing data on costs or QALYs will be multiply imputed. Costs and outcomes during the second year will be discounted in line with NICE guidance.^68^ Cost and QALY data will be combined to calculate an incremental cost-effectiveness ratio (ICER) and net monetary benefit (INMB) statistic,^69^ which will indicate whether the group CB programme is cost-effective compared with NICE thresholds of £20 000–£30 000 per QALY gained. Uncertainty in the point estimate of cost per QALY will be quantified by using bootstrapping methods to calculate CIs around the ICER and INMB. The probability that the group CB programme is cost-effective will be depicted using a cost-effectiveness acceptability curve, and one-way sensitivity analyses used to judge potential impact of other sources of uncertainty.

*Analysis of tutor experiences*: An inductive thematic approach will identify themes grounded in the participants’ data.^70^ After reading and re-reading the anonymised transcripts, significant statements will be extracted, coded, explored for links, built into overarching themes, and exemplified by participants’ quotations. A second qualitative researcher will independently analyse a subset of the transcripts and themes compared and agreed. The focus group and the interview findings will be integrated to provide a comprehensive account of tutors’ experiences.

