### Randomisation and allocation concealment

The research nurse will give each patient the next unique study identifier (ID) immediately after written consent. As patients are offered a choice of baseline visit dates/times, it is unlikely that ID allocation can be influenced. Whenever a centre has completed the baseline visits for a cohort of 10–16 participants, the central RAFT Trial Manager will email the ID list to Bristol Randomised Trials Collaboration (BRTC) who will manage the computer-generated randomisation using an access database. Randomisation will be stratified by centre and within each centre, by cohort (cohorts 1–4). Allocation will be 1:1, but in the event of an odd number, the CB arm will receive the additional patient. Upon receiving the arm allocations from Bristol, the research nurse will inform the consented participants by telephone, following guidelines to ensure a neutral conversation (ie, no implied potential benefit from a CB allocation), reminding participants they have already received usual care at baseline.

Patients randomised to the CB course but who are unable to attend the next course dates, will be offered a subsequent course, with a new baseline evaluation. Any changes to eligibility between screening and baseline (eg, fatigue less severe, medication change) will be noted for subgroup analysis, but the patient will proceed to randomisation. This reflects the pragmatic nature of delivering interventions to a population with recurrent but fluctuating fatigue.

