### Sample size

The baseline-adjusted effect size (0.77) for fatigue impact found in the original trial of CBT delivered by a clinical psychologist was 1.95 units (SD=2.7, 0–10 visual analogue scale).^32^ The current RCT of CB approaches delivered by rheumatology teams is powered to be able to demonstrate an average effect size across all participating centres of 75% of this (1.46 units, effect size 0.54)—clinically important, as it would reduce the number of patients falling below the fatigue criterion for trial entry by one-third. There are no published data on a minimal clinically important difference (MCID) for RA fatigue impact, but MCID for RA fatigue severity is 0.82–1.12 (0–10 scale).^41^ At a power of 90% and two-sided significance of 0.05, this requires 73 patients/arm. As we are interested in the average effect across all centres, we expect no loss of power as a result of randomising patients by site.^42^
^43^

There are two potential sources of clustering in the intervention arm: CB group effects and centre/tutor effects. In the original trial,^32^ the intraclass correlation coefficient (ICC) for the CBT group using the primary outcome was an estimated <0.00 001. No data exist for centre/tutor effects of CBT on RA fatigue, so we are taking an ICC value of 0.01 for groups clustered within centres.^44^ The resulting design effects increase the required sample size to 75/arm.

In the original RCT^32^ most attrition occurred after patients had completed their intervention, that is, loss to questionnaire completion. To minimise this, the primary outcome (fatigue impact, NRS) will be collected by telephone by the central RAFT team, missing data returns will be followed up, and patients who wish to withdraw will be asked if they would provide just their fatigue impact NRS. We anticipate obtaining 80% of primary outcome data (26 weeks). Longer term attrition is unknown, therefore, we have assumed 50% and a planned capacity to recruit up to 150 patients/arm, to maintain sufficient power at 2 years. A pragmatic approach to recruitment is needed to take account of natural variations in group size. Therefore, a target of seven centres, each running four CB courses with an average of six participants/group (n=168 in CB arm) provides contingency for some smaller groups.

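### The primary ANCOVA, as stated, names only the baseline value although randomisation is stratified by centre and cohort; the estimate stays unbiased, but some precision may be given away.

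*Protocol article*

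**What the plan says.** Under Randomisation and allocation concealment, the Protocol article states: "Randomisation will be stratified by centre and within each centre, by cohort (cohorts 1–4". With seven centres and four cohorts each, that makes 28 strata of 10 to 16 patients. Balance within a stratum is close: "Allocation will be 1:1, but in the event of an odd number, the CB arm will receive the additional patient".

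Under Analysis plan, the primary model is described as: "The primary intention-to-treat analysis will involve between-arm comparisons for the primary outcome fatigue impact (BRAF-NRS Impact) at 26 weeks, adjusted for baseline values". It is an ANCOVA fitted by linear regression, and secondary outcomes are handled in the same manner. Centre comes in through sensitivity analysis (2), described as "fitting multilevel mixed effects models to investigate any clustering effect from delivery in groups and centres", and through the repeated-measures models: "Clustering effects will be investigated by including CB group and centre IDs as additional levels". No model described contains cohort as a factor common to both arms. The treatment group exists only in the intervention arm, so it does not stand in for cohort.

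Sensitivity analysis (1) is "additional adjustment for any variables displaying imbalance at baseline". No criterion for imbalance is given.

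**The concern.** When allocation is balanced within strata, differences between centres and between calendar cohorts largely cancel out of the treatment contrast. A model with only arm and baseline score leaves that variation in the residual, so the calculated SE describes a less restricted randomisation than the one carried out. Confidence intervals come out wider than they need to be, and part of the benefit of stratifying goes unclaimed. The same applies to the secondary outcomes. It matters most at week 104, where the Sample size section assumes 50% attrition and the analysed number returns to the required 75 per arm.

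The covariate rule in sensitivity analysis (1) is a smaller issue. Under randomisation, baseline imbalance is chance. Selecting on it takes no account of how strongly a variable predicts outcome, and it leaves the choice to the observed data.

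**Working it through.** **Plan's own figures.** Inputs from the Sample size section: effect size 0.54, power 90%, two-sided 0.05.
- n per arm = 2 × (1.96 + 1.2816)² / 0.54² = 2 × 10.51 / 0.2916 = 72.1, so 73, as stated.
- Clustering: ICC 0.01 and average group size 6 give a design effect of 1 + (6 − 1) × 0.01 = 1.05. Applied to the intervention arm and averaged over arms: 73 × (1 + 1.05)/2 = 74.8, so 75, as stated.
- 75/(1 − 0.5) = 150 per arm. With 80% primary data, 150 × 0.8 = 120 per arm, or 240 patients.

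The point below does not change the sample size.

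**Effect of leaving out the strata.** Let v be the share of baseline-adjusted outcome variance lying between strata. With balanced strata, the baseline-only SE is too large by a factor of 1/√(1 − v), and actual type I error is 2 × (1 − Φ(1.96 × factor)). The article gives no value for v. Its 0.01 is for groups clustered within centres and is borrowed for the first row; the other rows are assumptions.

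| v | SE factor | Type I error |
|---|---|---|
| 0.01 | 1.005 | 4.9% |
| 0.05 | 1.026 | 4.4% |
| 0.10 | 1.054 | 3.9% |
| 0.15 | 1.085 | 3.4% |

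**Simulation check.** Set-up: 7 centres × 4 cohorts × 6 patients per arm, 20% missing at random, and 4,000 replicates per setting (Monte Carlo SE of a rejection rate about 0.35 percentage points). Assumptions: baseline–outcome correlation 0.5, and stratum variance split equally between centre and cohort. The comparison is between baseline-only ANCOVA and ANCOVA with fixed stratum terms.

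| v | Type I, baseline only | Type I, with strata | Mean SE, baseline only | Mean SE, with strata | Ratio |
|---|---|---|---|---|---|
| 0.01 | 5.0% | 5.1% | 0.1059 | 0.1066 | 0.993 |
| 0.05 | 4.1% | 4.3% | 0.1056 | 0.1043 | 1.012 |
| 0.10 | 4.3% | 5.1% | 0.1054 | 0.1015 | 1.038 |
| 0.20 | 3.5% | 5.3% | 0.1049 | 0.0958 | 1.095 |

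The direction agrees with the formula. The gain is a little smaller because missing outcomes disturb the balance and 28 fixed terms have a small cost of their own. At v = 0.01 there is nothing to gain.

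**Group clustering in the intervention arm.** The averaged design effect of (1 + 1.05)/2 = 1.025 means an SE that ignores it is too small by a factor of √1.025 = 1.012. If v is also 0.01, the net effect is 1.005/1.012 = 0.993, and type I error is 2 × (1 − Φ(1.96 × 0.993)), about 5.2%. The simulation of that setting gave 5.9% baseline-only and 5.6% with strata. Both are subject to the Monte Carlo error above, but both lie on the anti-conservative side. Stratum terms do not remove this clustering.

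**The case against.** The strongest objection is that this is a condensed article. It says the analysis will follow a separate Statistical and Health Economics Plan, which is not shown and may list centre and cohort as covariates; the article never says that baseline is the sole covariate. This limits the point to the article's wording. It does not remove it, because the article does more than stay silent: it states the primary adjustment and places centre in a sensitivity analysis. If the plan includes the strata, the article's description needs correcting.

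Second, the size is small or uncertain. This stands. At 0.01, the only ICC the article adopts, the effect is negligible, and nothing in the article supports 0.05 to 0.15. In partial answer, 0.01 was chosen for groups within centres, not for outcome differences across deliberately varied units recruited over two years.

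Third, primary power is not at risk. This also stands. With 120 per arm, 0.54/√(2/120) = 4.18, and Φ(4.18 − 1.96) is about 98.7% power before clustering. The statement "we expect no loss of power as a result of randomising patients by site" is not contradicted either.

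A reader might infer more than the text supports:
- That centre is ignored apart from one sensitivity model. It is also planned as a level in the repeated-measures models.
- That the imbalance rule distorts the primary interval. The rule reads "Sensitivity analyses will be conducted by (1) additional adjustment for any variables displaying imbalance at baseline", so it cannot reach the primary estimate.
- That this rule is the only planned covariate extension. The article also provides for adjusting for medication changes if necessary and for exploring predictors of outcome.

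**Conclusion.** The point holds as a mismatch between design and stated analysis: 28 randomisation strata, and a primary model that names none of them. Omitting the strata causes neither bias nor extra false positives. Its cost, all else equal, is an SE about 0.5% too wide at a stratum ICC of 0.01 and 2.6% to 8.5% too wide at 0.05 to 0.15, with type I error of 4.9% and 4.4% to 3.4% respectively. The mismatch itself is certain for the article's wording; its size is not, since the range above 0.01 is assumed.

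It would be tempting to conclude that the trial's actual type I error must fall below 5%. The documents do not support that. Group clustering in one arm acts in the opposite direction and, with both ICCs at 0.01, outweighs the effect of the omitted strata. That is a separate matter, and stratum terms will not settle it.

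The covariate rule in sensitivity analysis (1) is a minor secondary point with no bearing on the primary result.

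**What to change.** - **Primary ANCOVA and secondary-outcome models:** include centre and cohort within centre, either as fixed effects or as a random intercept for stratum, and state which. Define stratum by the cohort at randomisation, because patients who cannot attend their course may join a later one.
- **Repeated-measures models:** centre is already planned as a level; add cohort across both arms.
- **Sensitivity analysis (1):** replace selection by observed imbalance with a prognostic set named before unblinding. Baseline fatigue severity, pain and disease activity, already listed for the imputation model, are natural candidates.
- **If the unshown plan already does this:** bring the article's description into line with it.

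The cost is wording, plus at most 28 − 1 = 27 degrees of freedom from about 240 analysed patients. In the simulation with no stratum variance at all, fixed stratum terms raised the mean SE from 0.1057 to 0.1069 (0.1069/0.1057 = 1.011, about 1%). A random intercept should cost less. No data collection or sample size change is needed. Group clustering in the intervention arm must still be handled separately.

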**Trial registration number:**

ISRCTN: 52709998; Protocol v3 09.02.2015.

Strengths and limitations of this studyA pragmatic study testing a cognitive-behavioural intervention that could be delivered by the usual care team.A seven-centre trial targeting a broad population, thus, results likely to be widely generalisable.Patient impact is evaluated in a holistic fashion (eg, including valued life activities) alongside health economic evaluation.This pragmatic trial includes usual care throughout; any medication changes have the potential to alter fatigue and, therefore, the trial results (if changes differ between arms).

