### Usual care

The arthritis fatigue self-management booklet in common use^46^ was developed from this group's original RCT.^32^ It contains information on all the RAFT topics, a pull-out sample activity/rest chart to complete, and suggests that patients ask their rheumatology team for support with goal setting if necessary. This 32-page Arthritis Research UK free booklet is routinely provided by UK Rheumatology Units and discussed by nurses.

Usual care will be delivered to all patients at the baseline visit after consent and assessment, but prior to randomisation. The research nurse will spend 5–6 min discussing the booklet, using a standardised discussion guide, including that the booklet suggests patients might wish to request support from the rheumatology team. To minimise the risk of contamination between arms, the local nurse specialist managing such requests will try to not book a control patient in to see a clinician who is also an intervention tutor. This may be unavoidable in small teams, therefore, tutors will record any control patient appointments for fatigue support, for use in the analysis. Clinical care will continue as usual for both groups throughout; any medication changes will be recorded for potential subset analysis.

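### The further (26–104 week) analyses may adjust for, or subset on, medication changes made after randomisation, which can bias the estimated effect of adding RAFT to usual care

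*Protocol article*

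**What the plan says.** Three parts of the protocol article bear on this.

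- **Primary analysis (Analysis plan, part on clinical status).** The article fixes it as follows: "The primary intention-to-treat analysis will involve between-arm comparisons for the primary outcome fatigue impact (BRAF-NRS Impact) at 26 weeks, adjusted for baseline values". The only covariate-adjustment sensitivity analysis listed is "additional adjustment for any variables displaying imbalance at baseline". Neither mentions medication during follow-up.
- **Further analyses (next paragraph of the Analysis plan).** Repeated-measures mixed models use fatigue impact at 26, 52, 78 and 104 weeks. The same paragraph then says: "We will examine (and if necessary, adjust for) possible differences between arms for RA medication changes".
- **Usual care section.** "Clinical care will continue as usual for both groups throughout; any medication changes will be recorded for potential subset analysis".

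The strengths-and-limitations list after the abstract treats a difference between arms in medication changes as something that could alter the results. It does not consider that such a difference might itself result from the intervention.

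**The concern.** The stated aim is to compare RAFT added to usual care with usual care alone. Medication decisions during follow-up are part of that usual care. If the arms come to differ in them, there are two explanations.

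- **Chance.** The ITT comparison is already valid, and adjustment is not needed to remove bias.
- **Allocation.** The difference is then part of what adding RAFT does. Adjusting for it removes or distorts part of the effect that the trial set out to estimate.

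The data cannot reliably separate the two, and the adjustment is prompted by a difference between arms, which is the setting in which conditioning can do harm.

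An influence of allocation is plausible, though not demonstrated. Patients and clinicians are unblinded, and the tutors belong to the team that gives usual care. A shared cause of medication change and fatigue is also plausible from the article's Introduction, which says that RA medication is used to control inflammation and that inflammation is associated with fatigue.

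At stake is the third secondary aim, persistence of effect over two years, which these longitudinal models serve.

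**Working it through.** **Design figures.** The Sample size section gives a target of 1.46 units, SD 2.7, 90% power and two-sided 5% significance, and states 73 per arm. Check: 2 × [2.7 × (1.960 + 1.282) / 1.46]² = 71.9, so 72; with the rounded effect size of 0.54 the result is 73. The figure reproduces. It is not in dispute and serves only to anchor the illustration.

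**Assumed inputs.** The documents give no medication-change rates or effects. The assumptions are:

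- true total effect -1.46, SD 2.7;
- 20% to 40% of each arm with a change;
- effect of a change on fatigue of 0 or -1.0 unit;
- an unmeasured common cause, such as disease activity, worth 1.35 units of fatigue per SD, which either does or does not also drive medication changes.

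Where it does, a change occurs when the common cause plus an independent standard normal term exceeds an arm-specific threshold.

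**Formula.** In a linear model with arm and medication change (M),

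adjusted estimate = ITT estimate − γ × (p_CB − p_control),

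where p is the proportion with a change and γ is the within-arm difference in fatigue between patients with and without one. No shift arises if the rates are equal or if γ = 0.

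*Drug effect only* (γ = -1.0):

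- 30% control v 20% CB: -1.46 − (-1.0)(-0.10) = -1.56
- 40% v 20%: -1.46 − (-1.0)(-0.20) = -1.66
- 20% v 30%: -1.46 − (-1.0)(0.10) = -1.36

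*Common cause only*: γ = 1.35 × 0.7071 × [φ(z₁) + φ(z₂)] / [p₁(1−p₁) + p₂(1−p₂)], with φ the normal density at each arm's threshold.

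- 30% v 20%: γ = 0.9546 × (0.3477 + 0.2800) / (0.21 + 0.16) = 1.62; adjusted = -1.46 + 0.162 = -1.30
- 40% v 20%: γ = 0.9546 × (0.3863 + 0.2800) / (0.24 + 0.16) = 1.59; adjusted = -1.46 + 0.318 = -1.14
- 20% v 30%: γ = 1.62; adjusted = -1.46 − 0.162 = -1.62

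**Simulation** (2,000,000 patients per scenario, one time point):

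| Change rate, control v CB | Effect of change | Common cause drives change | ITT | Adjusted for change | No-change subset |
|---|---|---|---|---|---|
| 30% v 30% | 0 or -1.0 | no or yes | -1.46 | -1.46 | -1.46 |
| 30% v 20% | 0 | no | -1.46 | -1.46 | -1.46 |
| 30% v 20% | -1.0 | no | -1.46 | -1.56 | -1.56 |
| 30% v 20% | 0 | yes | -1.45 | -1.29 | -1.32 |
| 30% v 20% | -1.0 | yes | -1.46 | -1.40 | -1.42 |
| 40% v 20% | 0 | no | -1.46 | -1.45 | -1.46 |
| 40% v 20% | -1.0 | no | -1.46 | -1.66 | -1.66 |
| 40% v 20% | 0 | yes | -1.46 | -1.14 | -1.18 |
| 40% v 20% | -1.0 | yes | -1.46 | -1.35 | -1.38 |
| 20% v 30% | 0 | no | -1.46 | -1.46 | -1.46 |
| 20% v 30% | -1.0 | no | -1.46 | -1.36 | -1.35 |
| 20% v 30% | 0 | yes | -1.45 | -1.62 | -1.60 |
| 20% v 30% | -1.0 | yes | -1.45 | -1.52 | -1.49 |

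The simulation agrees with the formula to within about 0.01. The largest shift is 1.46 − 1.14 = 0.32 units.

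**Against the plan's own yardstick.** The Analysis plan takes a standardised effect above 0.5 as clinically meaningful. With 2.7 standing in for the pooled baseline SD, the threshold is 0.5 × 2.7 = 1.35 units, only 0.11 below the 1.46 target. An estimate of -1.29 gives 1.29 / 2.7 = 0.48, and -1.14 gives 0.42.

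**The case against.** The strongest reply is that little in the plan depends on this sentence.

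- **The primary result.** A reader might infer that the main 26-week result is compromised. The documents do not support that. The primary analysis is ITT with baseline adjustment, its covariate sensitivity analysis concerns baseline imbalance only, and the medication sentence sits with the further models. Nothing says that a medication-adjusted estimate would replace the ITT result. This stands in full.
- **Options, not commitments.** Adjustment is conditional and the subset analysis is only potential. A reader might also infer that bias is certain, but the table shows none when rates are equal, or when they differ and a change neither affects fatigue nor shares a cause with it. This stands too.
- **Size.** The largest shift, 0.32, is below one standard error of the difference: 2.7 × √(2/73) = 0.45, or 2.7 × √(2/120) = 0.35 with 80% of 150 per arm. That is true, but this error does not shrink as the sample grows, and the margin to the 0.5 threshold is small.
- **Mechanism.** The Introduction says that biological agents have only a small effect on fatigue, which weakens the route through the drug itself. The common-cause route does not need a drug effect.
- **The unseen plan.** The separate statistical and health economics plan may define the trigger and label the result. Their absence from an article is no fault. The option to adjust, however, is stated here as an analysis choice.

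Two neighbouring statements should not be drawn in. "Any changes to eligibility between screening and baseline (eg, fatigue less severe, medication change) will be noted for subgroup analysis" concerns events before randomisation, so the objection does not apply. "tutors will record any control patient appointments for fatigue support, for use in the analysis" might be read as a second instance of the same problem, but it names no covariate, exclusion or subset, and recording only control patients fits its purpose of tracking contamination.

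**Conclusion.** The point holds for the further analyses. As written, they allow the 26–104 week effect to be adjusted for a post-randomisation variable when the arms differ on it, and the Usual care section allows for subsetting on the same variable. Either estimate can depart from the total effect of adding RAFT to usual care, and the direction cannot be known from the documents.

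The illustrated shift of 0 to about 0.3 units on a target of 1.46 rests wholly on assumed change rates, drug effect and common cause, and on a single-time-point linear model rather than the planned repeated-measures model. It shows what is possible and does not forecast this trial's result. The exposure is confined to non-primary analyses, so this is a correction worth making rather than a threat to the trial's main conclusion.

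**What to change.** In the Analysis plan, replace the conditional adjustment with a statement that the ITT estimate without medication adjustment is the basis for inference at every time point, including the repeated-measures models, and that medication changes will be reported by arm descriptively.

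If a medication-adjusted or medication-change subset result is still wanted, label it exploratory, state its estimand (for example a mediation question, or a hypothetical one about the effect had no change occurred) and the assumptions needed, and say that it does not replace the ITT estimate. Bring the Usual care sentence on subset analysis into line.

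The cost is wording only. The medication data are already to be recorded, and neither the sample size nor the primary analysis changes. If the full analysis plan already limits the adjustment in this way, the article's wording need only be matched to it.
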